### Effective ingredients of primary preventive organizational interventions

The above outlines the need for primary preventive organizational interventions and a mixed methods evaluation, comprising both process and effect measures. But, what components should the intervention, or its application, comprise in order to be effective? In other words, what are effective ingredients for primary preventive organizational interventions in the educational sector? To the best of our knowledge, the current study is the first of that type in that sector. Therefore, we could only argue theoretically what would be the effective ingredients that bring about the desired effect. We propose hereafter that joint ownership (i.e. participation) and occupational self-efficacy play an important role in bringing about the effect on job demands and resources, and need for recovery and vitality (Figure 1).

**Figure 1 F1:**
[figure not shown]
Conceptual model.

First, the intervention should be designed in a manner that resembles the tradition of participatory action research (PAR) [39]. Essential in using PAR to design effective stress interventions in the workplace is active participation of stakeholders and (long term) collaboration between researchers and stakeholders [32]. By establishing a participatory group and making use of management’s and worker’s knowledge, skills and perceptions, a feeling of joint ownership of both problems and solutions is created and the participants learn-by-doing how to discuss issues in the workplace. Therefore the intervention should be considered ‘bottom-up’. Nielsen and colleagues have pointed to the relative importance, but rare discussion of joint ownership [40]. This intervention will contribute to that discussion.

Second, the intervention should target occupational and organizational efficacy. Self-efficacy is ‘the belief in one’s own ability to master specific domains in order to produce given attainments’ [41-43]. Occupational self-efficacy refers to beliefs in one’s own ability in the specific domain of work. Self-efficacy can be enhanced in several manners, but the most effective way is through mastery experiences [44]. By taking part in the intervention, it is assumed that workers experience mastery and self-efficacy is thus influenced. A recent study showed that job demands and job resources partially mediated the relation between occupational self-efficacy (or: work self-efficacy) and burnout [45]. The intervention should elaborate empirically on the results of the Consiglio and colleagues article [45]. There is an intervention that comprises these supposedly effective ingredients. The intervention has been developed by a Dutch consulting firm and applied over a hundred times to public and private organizations in The Netherlands in the past decade. That intervention will be tested in the current study.

In sum: we propose an organizational level, primary preventive stress management intervention, aimed to alter the sources of work-related stress by changing the design, management and organization of work [46,47] and to be evaluated by an effect evaluation including organizational outcomes and a process evaluation including process variables related to intervention outcomes. Both the bottom-up intervention, as well as the mixed methods design make this study innovative and a contribution to existing knowledge to the field of organizational interventions.

### Study objectives

The current study tests a participatory, primary preventive organizational level intervention (i.e. a participatory action approach) that targets and engages all workers in the primary process of schools. Participation of employees and managers is supposed to result in increased occupational self-efficacy and organizational efficacy. The application of the intervention will yield work-oriented solutions tailored to the school setting, changing (the balance between) specific job demands and job resources. By improving the balance between job demands and job resources, it is expected to improve precursors of burnout (i.e. high need for recovery, low vitality) in the long run. The central research question is thus: is an organization focused stress management intervention based on participatory action effective in reducing the need for recovery and enhancing vitality in school employees in comparison to business as usual?

In this article we present the design of a controlled trial in two vocational schools in the Netherlands, wherein the participatory action approach and resulting work-oriented solutions are tested empirically.

## Methods/Design

A quasi-experimental field study is conducted to determine the effectiveness of the participatory action approach (phase 1: needs assessment) and tailored work-oriented solutions (phase 2: implementation plan), compared to business as usual. The study is designed as a controlled trial (CT) with mixed methods (quantitative and qualitative) and three measurement moments: T0 at baseline (quantitative measurement), T1 at six months (quantitative and qualitative measurement) and T2 at 18 months (quantitative and qualitative measurement) (Figure 2). A CT is necessary to control for random changes, although the researchers are well aware of the fact that they are conducting a *social* experiment and that causal relations are thus embedded in complex contexts [38]. Randomization to experimental group (intervention group) or control group is practically impossible in this project, as often in organizational level workplace interventions [38], due to the aspirations of participating schools. Both schools participate in the study because they aim to solve a problem or reach a goal within a specific department of the school. The experimental groups were thus selected by the schools. To reduce the negative impact of selection bias, the control groups are selected by the researchers according to the ‘general control’ matching principle (or: frequency distribution control) [48]. Matching criteria are: department size (at least 150 employees), mean age of employees, and type of work (i.e. teaching vocational students and not secondary school pupils). Since the assignment to groups was out of our control, we will examine in the analyses whether propensity score matching is necessary. By applying the statistical technique of propensity score matching, the effect of the intervention can be estimated accounted for covariates that predict receiving the intervention. This way we expect to nullify potential confounding bias [49].

**Figure 2 F2:**
[figure not shown]
Flow chart of design, measurements, population and intervention program.

### Setting

The project is conducted in two institutions for vocational education (in Dutch: *Middelbaar Beroepsonderwijs* (MBO)) in the western (Alkmaar, Hoorn and Egmond) and northern (Leeuwarden and Heerenveen) Netherlands.

#### Study population

The intervention is applied to one department in both schools, another department in the same school is matched by the researchers as a control group. The target group of the project are teaching and non-teaching (i.e. educational and administrative support staff) employees in two vocational education institutions and their managers. Employees who work within the vocational institution, but do not teach at a secondary vocational level are excluded from the study population (e.g. teachers in general secondary education for adults). All participants are asked to sign an informed consent at baseline.

#### Sample size

The sample size calculation is based on the number of cases required to detect a small (Cohen’s d = 0.2) effect on the primary outcome vitality, as measured with the 3-item subscale of the 9-item version of the Utrecht Work Engagement Scale (UWES-9) [50]. The baseline mean vitality score (range 0–6) is assumed to be 4.01 (SD = 1.14), based on the scores of 9,679 Dutch and Belgian employees [51]. A 5% increase of the mean score on vitality in the intervention group after 12 months is considered relevant and feasible (4.21; SD 1.20).

The required sample size is then 385 (193 for both intervention and control group; thus 97 per intervention and control group per school), assuming a significance level (α) of 0.05, two-sided tests and power (1-β) of 0.80 [52]. A non-response and loss to follow-up of 35% is taken into account, so that a total sample size of 600 is needed.

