### Data analysis

#### Effect evaluation

The effectiveness of the intervention on primary outcomes (need for recovery and vitality) and secondary outcomes at short term (T1), long term (T2) and corrected for baseline values, will be established by multilevel analyses. Repeated measurements on the worker-level and clustering of observations can thus be taken into account. The data will be analyzed at three levels: 1) worker, 2) department, and 3) school. Both crude and adjusted linear and logistic regression analyses will be conducted. The intention-to-treat principle is leading in all statistical analyses, meaning that the analyses are based on the initial treatment assignment and not on the treatment eventually received. However, per-protocol analysis will also be conducted, restricting the comparison to the ideal participants, in this study: participants that report taking part in at least two of the three steps of the needs assessment.

Multilevel analyses wherein T1 functions as the dependent variable, will be adjusted for possible confounding factors (e.g. experience, overtime). These variables will also be checked for effect modification at all measurement moments.

For all analyses, a two-tailed significance level of p < 0.05 will be considered statistically significant. The multilevel analyses will be conducted by means of MlwiN 2.0; linear and logistic regression analyses will be performed using SPSS 17.0 (SPSS Inc. Chicago, Illinois, USA).

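### The 80% power claim rests on a worker-level calculation with no allowance for clustering, although whole departments, only two per arm, are allocated

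*Protocol article*

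**What the plan says.** The Sample size section of the protocol article opens with its basis: "The sample size calculation is based on the number of cases required to detect a small". The target is a standardised difference of 0.2 in vitality. The section assumes that "The baseline mean vitality score (range 0–6) is assumed to be 4.01 (SD = 1.14") and that a 5% rise "in the intervention group after 12 months is considered relevant and feasible (4.21; SD 1.20"). Error rates enter in these words: "assuming a significance level (α) of 0.05, two-sided tests and power (1-β) of 0.80". The result is reported in one sentence: "The required sample size is then 385 (193 for both intervention and control group; thus 97 per intervention and control group per school"). The only inflation is for 35% non-response and loss to follow-up, which gives 600.

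The Study population section fixes the unit of allocation: "The intervention is applied to one department in both schools, another department in the same school is matched by the researchers as a control group". That makes four departments, two per arm. The limitations text in the Discussion repeats that departments are allocated to conditions.

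The Effect evaluation section plans a multilevel analysis with worker, department and school as levels, and gives the reason: "Repeated measurements on the worker-level and clustering of observations can thus be taken into account".

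**The concern.** The analysis section accepts that workers in one department are correlated. The sample size section treats them as independent: 385 follows from an individual-level effect size, alpha and power, and is then merely divided over the four departments. A correctly fitted multilevel model will therefore give a wider standard error than the power calculation assumed.

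Two things are at stake. A non-significant result on vitality would be read against a claimed 80% power that the design does not have. The sponsor might also work on response rates, although at most plausible ICC values the limit is the number of departments.

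**Working it through.** **Inputs from the protocol.** d = 0.2; two-sided alpha 0.05; target power 0.80; 193 per arm; 97 per department; two departments per arm (2 × 97 = 194 analysed per arm); planned total 600, or 150 per department; minimum department size 150 (matching criteria in Methods/Design).

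**Assumption.** The protocol gives no ICC. I use 0.005, 0.01, 0.02 and 0.05.

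**Step 1: the plan's own figure, independent workers.** n per arm = 2(1.96 + 0.842)²/0.2² = 393, so 786 in total. The stated 385 (193 per arm) is not reproduced. At 193 per arm, power = Φ(0.2·√(193/2) − 1.96) = about 50%. This arithmetic error is separate from clustering, but it sets the starting point for the combined figures. The loss adjustment is consistent: 385/0.65 = 593, rounded to 600.

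**Step 2: design effect.** DE = 1 + (97 − 1)·ICC. Effective n per arm = 194/DE.

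**Step 3: clustering alone.** Suppose 193 per arm did give 80%, so that the expected z is 1.96 + 0.842 = 2.80. Clustering divides it by √DE. Example at ICC 0.01: 2.80/√1.96 = 2.00, so power = Φ(2.00 − 1.96) = 52%.

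**Step 4: both faults together.** The expected z is 0.2·√(effective n/2). Example at ICC 0.01: 0.2·√(99/2) = 1.41, so power = Φ(1.41 − 1.96) plus the opposite tail = 29%. This treats the variance as known. Four department means in two arms leave 4 − 2 = 2 degrees of freedom, and a t-test on those means with the same noncentrality gives the lower row in the table.

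**Step 5: ceiling with unlimited workers in the same four departments.** Effective n per arm tends to 2/ICC, so the expected z tends to 0.2/√ICC.

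| | ICC 0.005 | 0.01 | 0.02 | 0.05 |
|---|---|---|---|---|
| Design effect | 1.48 | 1.96 | 2.92 | 5.80 |
| Effective n per arm | 131 | 99 | 66 | 33 |
| Power, clustering alone from a true 80% (z) | 63% | 52% | 37% | 21% |
| Power, both faults (z) | 37% | 29% | 21% | 13% |
| Power, both faults (t, 2 df) | 16% | 14% | 11% | 8% |
| Ceiling, unlimited workers (z) | 81% | 52% | 29% | 15% |
| Ceiling, unlimited workers (t, 2 df) | 36% | 22% | 14% | 9% |

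**Step 6: where more workers stop helping.** Setting 0.2/√ICC = 2.80 gives ICC = (0.2/2.80)² = about 0.005. With 2 df the noncentrality needed for 80% is about 5.65, so the threshold is (0.2/5.65)² = about 0.001.

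**Step 7: the practical limit.** If all 600 responded (150 per department), DE would be 1 + 149·ICC. Power by z would be about 46% at ICC 0.005 and 34% at 0.01.

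**The case against.** **The multilevel model already deals with clustering.** It corrects the standard error. It does not supply the power claimed in the sample size section.

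**The crude ICC may be too pessimistic.** The analysis corrects for baseline values, both departments of a pair sit in the same school, and controls are matched on size, mean age and type of work. The residual between-department correlation may therefore be lower than the crude one. This stands as a reason to show a range. However, the sample size section claims no such gain, and analysing the two schools as pairs leaves only 1 degree of freedom.

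**More respondents could help.** A reader might infer that no number of workers could ever restore 80%. The documents do not support that, because they give no ICC. At 0.005 the z ceiling is 81%, and below that value enough workers could in principle suffice by z.

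**Not all of the shortfall is due to clustering.** A reader might set 80% against 37% and blame clustering for the whole gap. That is wrong: the 37% starts from the roughly 50% that 193 independent workers per arm provide. The row for clustering alone shows its separate share.

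**The protocol is open about its design.** It calls randomization practically impossible, lists small samples as typical of this study type and names the quasi-experimental design as a limitation. None of this corrects the 80% figure or says that the number of departments limits power.

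**Conclusion.** The point holds. The protocol states a complete power calculation that conflicts with its own allocation and analysis, so this is not a detail left to an analysis plan. For d = 0.2 and an assumed ICC of 0.005 to 0.05, clustering alone would reduce a true 80% to between 63% and 21%. With the separate arithmetic error included, power is between 37% and 13% by z and between 16% and 8% on 2 degrees of freedom. The z figures are lenient, because they treat the between-department variance as known.

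The claim about adding workers is conditional. With two departments per arm it holds once the ICC exceeds about 0.005 by z, or about 0.001 with 2 degrees of freedom. That the calculation omits clustering is certain from the text; the size of the loss depends on an ICC that the protocol does not give.

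**What to change.** Rewrite the Sample size section as follows:

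- Drop the 80% claim.
- Give the power for independent workers as the starting point (about 50% at 193 per arm and d = 0.2).
- Restate power, or the detectable difference, over a declared ICC range. Use the design effect 1 + (m − 1)·ICC with m about 97 and a t reference with about 2 degrees of freedom. A design effect with a z test alone would still print too favourable a figure.
- If a gain from baseline adjustment or within-school pairing is claimed, state the assumed residual ICC and the degrees of freedom that remain.
- State that two departments per arm are the main limit on power unless the ICC is very small.
- State that a non-significant result will be interpreted through its confidence interval and called inconclusive, not taken as evidence of no effect.

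The cost is a less favourable stated power. Allocation, data collection and the planned multilevel analysis stay as they are.

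### The stated total of 385 (193 per arm) does not follow from d = 0.2, two-sided alpha 0.05 and 80% power; those inputs need about 394 per arm, and the stated means and SDs about 539

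*Protocol article*

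**What the plan says.** All the inputs are in one paragraph of the protocol article (Methods/Design, Sample size).

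- Target: to "detect a small (Cohen’s d = 0.2) effect on the primary outcome vitality".
- Reference values: "The baseline mean vitality score (range 0–6) is assumed to be 4.01 (SD = 1.14"), with a 5% rise that "in the intervention group after 12 months is considered relevant and feasible (4.21; SD 1.20").
- Error rates: "assuming a significance level (α) of 0.05, two-sided tests and power (1-β) of 0.80".
- Result: "The required sample size is then 385 (193 for both intervention and control group; thus 97 per intervention and control group per school").
- Allowance for loss: "A non-response and loss to follow-up of 35% is taken into account, so that a total sample size of 600 is needed".

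The paragraph mentions no baseline correlation, no gain from repeated measurement and no design effect. Under Study objectives, the research question is a between-group one: whether the intervention is effective "in reducing the need for recovery and enhancing vitality in school employees in comparison to business as usual".

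**The concern.** The paragraph gives a complete calculation, and its result can be checked against its own inputs. It fails in two ways.

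1. The total is about half of what d = 0.2 requires at the stated alpha and power.
2. The means and SDs offered in support of d = 0.2 imply a smaller standardised effect.

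Vitality is one of two primary outcomes and the only one used for sizing. If the 80% is taken at face value, a non-significant result on vitality carries more weight against the intervention than the design can support. The effect that the protocol calls relevant would be missed about as often as found, on the simplest reading of the plan.

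**Working it through.** **Inputs** (all from Sample size): d = 0.2; means 4.01 and 4.21; SDs 1.14 and 1.20; two-sided alpha 0.05; power 0.80; 193 per arm; 35% loss; 600 in total. Normal quantiles: 1.960 and 0.842.

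**1. What 385 refers to.** The split is explicit: 2 × 193 = 386 and 4 × 97 = 388. The loss step also treats 385 as the total: 385 / 0.65 = 592.3, rounded up to 600, and 600 × 0.65 = 390 analysed (195 per arm). That step is sound. So 385 cannot be read as a per-arm figure.

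**2. Size for d = 0.2.**
n per arm = 2 × (1.960 + 0.842)² / 0.2² = 392.4. The t-test version gives 393.4, so 394 per arm and 788 in total. The stated 385 is 49% of that. With 35% loss, 788 / 0.65 = 1,213.

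**3. Effect size from the printed means and SDs.**
Pooled SD = √((1.14² + 1.20²) / 2) = 1.170.
d = (4.21 − 4.01) / 1.170 = 0.171.
The t-test version needs 538.5, so 539 per arm and 1,078 in total. With 35% loss, 1,078 / 0.65 = 1,659.

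**4. Power with 193 per arm** (independent workers, one follow-up, no baseline adjustment).
- d = 0.2: 0.2 × √(193/2) = 1.965, almost equal to the critical value of 1.960, so power is 50%.
- d = 0.171: 0.171 × √(193/2) = 1.68, so power is 39%. Using SD 1.20 or SD 1.14 alone gives 37% or 40%.
- With 195 per arm (390 analysed) the figures are again 50% and 39%.

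**5. Smallest effect with 80% power at 193 per arm.**
(1.960 + 0.842) × √(2/193) = 0.285 (t-test: 0.286). In points, 0.286 × 1.170 = 0.33, and 0.33 / 4.01 = 8%, against the 5% named in the plan.

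**6. Other readings of the two-group formula.**
- One-sided at d = 0.2: 310 per arm, 620 in total; the text says two-sided.
- Paired or one-sample at d = 0.2: about 199; the question is a comparison with business as usual.
- All 600 analysed with no loss: 69% power at d = 0.2 and 55% at d = 0.171.

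None gives 385 in total at 80% power.

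**7. Sensitivity to what the paragraph leaves out.** The protocol article gives no correlation and no intraclass correlation (ICC), so these are assumed ranges.

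Baseline adjustment multiplies the variance by 1 − r² (one follow-up, 193 per arm, no clustering):

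| r | Power, d = 0.2 | Power, d = 0.171 |
|---|---|---|
| 0 | 50% | 39% |
| 0.3 | 54% | 42% |
| 0.5 | 62% | 49% |
| 0.7 | 78% | 65% |

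For 193 per arm to give 80% power, r must be about √(1 − 193/393) = 0.71 at d = 0.2, or √(1 − 193/538) = 0.80 at d = 0.171.

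Clustering multiplies the variance by 1 + (97 − 1) × ICC. That is 1.96 at ICC 0.01 and 5.8 at ICC 0.05. At ICC 0.01 with r = 0.7 the two nearly cancel: (1 − 0.49) × 1.96 = 1.00, which puts power back at about 50% and 39%. At ICC 0.01 with no baseline credit, power is about 29% and 22%.

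**The case against.** The strongest defence is that the 50% and 39% are not the power of the planned analysis. Under Effect evaluation the protocol plans multilevel models corrected for baseline values, with repeated measurements on each worker. With r near 0.7, power at d = 0.2 comes close to 80%. If the effect were averaged over both follow-ups with every correlation equal to 0.5, the variance factor would be (1 + 0.5)/2 − 0.5² = 0.5, and about 197 per arm would do at d = 0.2.

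Part of this stands: the two figures must be labelled as unadjusted. It does not rescue the paragraph. The Sample size section claims no such credit and sizes for a single time point, and the analysis section asks for short-term and long-term effects, not their average. At d = 0.171 the averaged version would still need about 538 × 0.5 = 269 per arm. The same analysis section names department and school as levels, and clustering pulls power down. The unadjusted figures are therefore neither a best nor a worst case.

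A reader might also infer how the error arose: that a per-arm figure was taken as the total, or that the raw 0.20 points was mistaken for a standardised 0.2. The document supports neither. The number 385 is near 393, but it is matched exactly by leaving out the power term: 4 × 1.96² / 0.2² = 384.2, and per arm 2 × 1.96² / 0.2² = 192.1, which round up to 385 and 193. Likewise, 0.171 becomes 0.2 when rounded to one decimal. The mismatch is certain; its origin is not.

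The length limits of an article are no answer. Nothing was left to another document here: the inputs and the result are both printed, and they disagree.

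**Conclusion.** The stated size and power are wrong as written. At the stated d, alpha and power the requirement is about 788 analysed workers, not 385. At the stated means and SDs it is about 1,078. The 35% loss step is correct, but it starts from the wrong number.

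The power figures of about 50% and 39%, and the detectable d of about 0.29, rest on three assumptions: a two-group comparison at one follow-up, independent workers, and no baseline adjustment. It would go too far to say that the planned multilevel analysis itself has 50% or 39% power. That depends on a baseline correlation and an ICC that the protocol does not give, and they act in opposite directions. What can be said is that nothing in the Sample size section supports 80%.

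**What to change.** Rewrite the Sample size paragraph:

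- Keep the 600 invited, with about 390 analysed.
- Remove the statement that this gives 80% power for d = 0.2.
- Make the effect size agree with the means and SDs: either state d = 0.17 for 4.01 against 4.21, or change the target difference.
- Restate what the size delivers, labelled as unadjusted and unclustered: about 50% power at d = 0.2 and 39% at the stated means and SDs, or 80% power for about 0.29 SD (0.33 points).
- If credit is taken for the planned baseline correction, state the assumed correlation and show a range. For r from 0.5 to 0.7 this is about 62% to 78% at d = 0.2, and 49% to 65% at d = 0.171.
- Beside it, show the effect of an assumed ICC within the four departments. For example, an ICC of 0.01 with about 97 per department gives a design effect of about 1.96.

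The cost is a less favourable power statement. No participants are added, and neither the design nor the analysis changes.
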